### Study setting

The study will be conducted in a number of small towns in the remote Northern Peninsula Area (NPA) of Far North Queensland. In the 2011 Census the population of the NPA was estimated at 1046 and is comprised of 52.8 % females and 47.2 % males. The median/average age of the NPA population is 22 years, 15 years below the Australian average. 98.7 % of people living in these communities were born in Australia.

English is spoken as first language by 22.7 % of the population, Yumplatok (Torres Strait Creole) by 64.9 %, Kalaw Kawaw Ya/Kalaw Lagaw Ya by 1.8 and 0.3 %. Sixty eight percent of residents are employed full time, and 21 % are working on a part time basis. The NPA has an unemployment rate of 7 %. The median individual income is AUD554.00 per week and the median household income is AUD1, 179.00 per week (AUD = Australian Dollar).

### Study participants

All children (approximately 600–650) attending the two primary and one secondary school campuses will be invited to participate in the intervention study. These children will be 4–17 years of age, and almost all are Indigenous. As all children in the community will be invited to participate a sample power calculation was not performed.

### Intervention

The proposed “Big Bang” preventive intervention is to firstly reduce the pathogenic bacterial load, then seal grooves on posterior (molar) teeth, and thirdly to strengthen the tooth structure.

Oral health promotion will essentially educate children regarding appropriate health behaviours to maintain oral health, with emphasis on the importance of toothbrushing with fluoridated toothpaste, healthy eating habits, emphasising the role of sugar in the tooth decay process, and the importance of reducing both the quantity and frequency of sugary products in the diet.

Prior to the annual intervention the research team will undertake clinical examination of all consenting school-age children to assess dental caries experience. A team comprising of a dentist and/or oral health therapist will treat all existing tooth decay and other oral health problems. Each child will receive the preventive intervention when other treatments are completed.

Prior to the treatment of existing disease, we will investigate saliva of the participants as a component of caries risk assessment. Saliva will be collected using commercially available test kits for measurement of flow rate, pH, buffering capacity and then cultured for bacterial assessment [33]. The number of teeth, fillings and other retentive sites in mouth influence the bacterial load and a high count of bacteria in dental plaque correlates with salivary bacterial counts, making it possible to assess saliva for cariogenic microbes [34, 35]. Such kits use selective media for mutans streptococci and for lactobacilli.

### Primary outcome variable

The International Caries Detection and Assessment system (ICDAS-II) for clinical caries diagnosis will be used to record caries experience and to determine incidence [36]. This will be measured annually across the 3 years of the study, at baseline and after years 2 and 3 of the project.

ICDAS-II consolidates features of several caries classification systems into one universal system using a six-point ordinal scale ranging from non-cavitated to extensive cavitated lesions to describe any signs of past or present caries activity. Unlike World Health Organisation (WHO) caries detection criteria, ICDAS-II allows the detection of initial/non-cavitated carious lesions, and is thus considerably more sensitive, whilst allowing the extraction of data comparable to previous surveys which used WHO criteria [37].

### Secondary outcome variables

General Child Quality of Life, the social impact of oral disorders and Oral Health-Related Quality of Life (OHRQoL) will be measured at baseline and at years 2 and 3. Existing validated and reliable instruments will be used (CHU-9D [38], OHIP-14 [39] and Child-OIPD [40]), appropriately modified for our participants.

The retention of the fissure sealants at the follow-up periods will be assessed, and recorded. Saliva of the participants will be collected again in years 2 and 3. Findings will be compared to baseline to assess the impact of the less frequently applied anti-bacterial component of the intervention.

Resources use and costs of providing the intervention will be recorded throughout the intervention period. Resource use and costs to participants to receive the intervention (e.g. time off work to bring the child to the clinic) will be recorded as well as any emergency treatment required between annual visits by the team. Emergency treatment includes travel to the nearest dental facility, the Royal Flying Doctors Service call-outs, local GP visits for antibiotics and analgesia, and so forth.

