The proposed study will implement a novel dental caries preventive intervention in children to firstly reduce the pathologic bacterial load using an oral anti-septic, secondly seal the part of the tooth most prone to decay with a fissure sealant, and thirdly to strengthen the tooth structure with a fluoride varnish, all during a single annual visit, in a rural remote Indigenous community in Far North Queensland, Australia. While there are data on the effectiveness of the three specific interventions, we have developed a novel approach to assess a less frequent combined application of these interventions. Importantly, we will assess its effectiveness and its cost effectiveness to determine the value for money of the service.

The team believes that the current suggested frequency 2–4 times per year for these preventive interventions is not possible, or sustainable, in poorly-resourced, remote communities and is proposing an alternative strategy requiring fewer resources to address the burden of dental decay in children.

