One of the reasons for the improved oral health status could be due to fluoridation of the local water supplies. Whilst the economic viability of water fluoridation for a small community such as this might be questioned, we posit the costs are outweighed by the significant caries reduction in both the deciduous and permanent dentitions as found in our study [18]. Moreover, the fluoridation plant has functioned erratically since being implemented and has been out of operation since April 2011 following a lightning strike. The likelihood that the water will again be fluoridated is uncertain due to budget constraints and because the 2012–2015 Queensland State Government legislated to give local governments across the State the power to decide to fluoridate or not. Dental caries rates may again increase in the absence of water fluoridation. It will be crucial to investigate alternative models to ensure improvements in dental caries incidence in this resource-constrained community. The envisaged dental prevention model will essentially reduce the microbial load with the topical disinfectant, povidone iodine [10]; inhibit biofilm adherence to susceptible sites by application of fissure sealants [19] and reduce the susceptibility of the tooth to demineralisation by acids generated in the microbial biofilm by the application of a fluoride varnish [9, 20]. Measures of local fluoride concentration [20] and of oral mutans streptococci counts return to baseline after a few months [21], so that most reported studies have used regular re-applications (2–4 times per annum), which would be difficult to implement in remote settings lacking appropriately trained personnel and resources. Fissure sealants, on the other hand, have excellent longevity [19].

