## Methods

### Study design

This is a longitudinal preventive intervention study. All school children in the NPA will be invited to participate. As it is unethical to withhold any proven intervention from any child, no control group will be created. Children who do not consent to participate may be natural controls if they consent to a dental examination at the end of the study. The actual caries increment in the children who participate will be compared to the expected caries increment modelled on oral health surveys carried out in this community in 2004 (pre-water fluoridation); in 2012 (by the Griffith University team post-partial water fluoridation) and 2015 (baseline survey for this study).

All consenting children will undergo a detailed head, neck and dental clinical examination and complete a questionnaire on their basic demography (gender and age), residential history (exposure to fluoridated drinking water), own general and oral health perceptions; oral health behaviours, attitudes and knowledge; dental visits; diet and oral health-related quality of life.

All active disease will be treated prior to implementing the dental caries preventive intervention. In years 2 and 3 of the study, all participating children will be invited to return for a dental examination, treatment of new incident disease and repeat of the prevention regime.

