## Discussion

Tooth decay in rural Indigenous children is unacceptably high, and their general and oral health-related quality of life is significantly compromised. There is an urgent need to reduce the burden of dental decay in these communities, by implementing effective, cost-effective, feasible and sustainable dental prevention programs. Expected outcomes of this study include improved oral and general health of children within the community; an understanding of the costs associated with the intervention provided, and its comparison with the costs of allowing new lesions to develop, with associated treatment costs. The work will benefit Indigenous children and reduce disparities. If found to be effective and cost-effective in reducing dental caries, this initiative could be implemented in similar communities elsewhere.

The study will provide longitudinal data on dental caries prevalence and incidence and OHRQoL for remote Indigenous children, a group often neglected or under-represented in national oral health surveys. The study will further provide information on the oral hygiene practices and diet (sugar) of these children. Data on the impact of a less frequent antibacterial intervention on the presence of the main dental caries associated bacteria in the saliva, as well as the retention of fissure sealants, will be reported.

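### Saliva taken at the annual visits can show only whether counts stay lower about 12 months after the whole programme, not what the antiseptic component did

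*Protocol article*

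**What the plan says.** All references are to the protocol article.

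- **Application.** The Background describes the antiseptic, the sealant and the varnish as given together, "all during a single annual visit, in a rural remote Indigenous community in Far North Queensland, Australia".
- **Baseline sample.** The Intervention section says: "Prior to the treatment of existing disease, we will investigate saliva of the participants as a component of caries risk assessment". The preventive package comes later: "Each child will receive the preventive intervention when other treatments are completed". Baseline saliva therefore precedes both the restorative work and the antiseptic.
- **Follow-up samples.** Secondary outcome variables says: "Saliva of the participants will be collected again in years 2 and 3". Study design describes the visits: "In years 2 and 3 of the study, all participating children will be invited to return for a dental examination", followed by treatment of new disease and then a repeat of the regime. No saliva sample between annual visits is described.
- **Stated purpose.** Secondary outcome variables says: "Findings will be compared to baseline to assess the impact of the less frequently applied anti-bacterial component of the intervention". The Discussion promises to report "Data on the impact of a less frequent antibacterial intervention on the presence of the main dental caries associated bacteria in the saliva".
- **Duration of effect.** The Background section on the burden of caries says that "oral mutans streptococci counts return to baseline after a few months" and gives this as a reason why most studies re-apply two to four times a year. The reference cited there is also listed among the povidone-iodine studies in the section on that agent.

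**The concern.** The sampling times, the comparison and the conclusion to be drawn are all fixed in the text, and they do not fit together. The conclusion is about one component, the antiseptic. The samples fall well after the time by which the document itself says the bacterial effect has gone.

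Two inferences are at stake. If counts at follow-up equal baseline, that is what the Background predicts both for an antiseptic that suppressed bacteria for some months and for one that did nothing. If counts are lower, several other things have changed since baseline and there is no comparison group to separate them. Neither result informs a statement about the antiseptic itself, yet such a statement is what the two sections promise.

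**Working it through.** The protocol gives no effect size, power or test for saliva, so there is no figure to reproduce. The point rests on timing and attribution. The arithmetic only illustrates it.

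**1. Interval from application to sample.** The Analysis section measures increments over 2015–2016 and 2016–2017, and Secondary outcome variables speaks of annual team visits. At each return visit the regime is repeated after examination and treatment, and the Intervention section places saliva collection before treatment. This gives about 12 months from last application to sample. The interval is inferred: the follow-up text does not say that saliva precedes re-application.

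**2. Children seen only at the second follow-up.** The Analysis section expects some children with a baseline and only a year 2 follow-up. That section counts follow-up years, so this is the third project year, 2017. Such a child was last treated in 2015, and the sample comes about 24 months after the only application. It is a different quantity from a 12-month sample.

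**3. What changes between baseline and follow-up samples.** Decay is treated, sealants and varnish are placed, diet and hygiene education is given, and the children are older. The Intervention section itself says that restorations and plaque-retaining sites affect bacterial load. Study design states that no control group is created. Children who decline may serve as natural controls if they agree to a dental examination at the end, but no saliva is described for them.

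**4. Illustration of the residual effect.** Assumptions, none of them in the protocol: exponential return to baseline, with a share *f* of the initial effect left at *T* months. The share left at 12 months is r = f^(12/T).

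| T (months) | f = 5% | f = 10% |
|---|---|---|
| 2 | 0.0000016% | 0.0001% |
| 3 | 0.0006% | 0.01% |
| 4 | 0.0125% | 0.1% |
| 6 | 0.25% | 1% |

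The most favourable cell is 0.10^(12/6) = 0.01. The year 3 sample may follow two applications. If the effects add, that gives r + r² = 0.01 + 0.0001 = 0.0101, so the picture does not change.

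**5. Could the study see such a residual?** Assume a very large initial reduction of 2 SD (SD of the paired change). The residual is then at most 2 × 0.01 = 0.02 SD. The smallest paired change detectable with 80% power at two-sided 0.05 is (1.960 + 0.842)/√n:

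- n = 300: 2.802/17.32 = 0.16 SD
- n = 600: 2.802/24.49 = 0.11 SD

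Power for 0.02 SD is Φ(0.02√n − 1.960) + Φ(−0.02√n − 1.960):

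- n = 300: about 6%
- n = 600: about 8%

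Both are close to the 5% false positive rate. The 600 is the lower end of the 600–650 children to be invited; the 300 is an assumed lower participation. The 0.05 level is stated for the caries comparison and assumed here for saliva.

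**The case against.** The strongest reply is that the stated target is the *less frequently applied* component. The study asks whether an annual schedule leaves any benefit where two to four applications a year are not feasible. A sample at the end of the interval answers whether a reduction persists under that schedule. This stands. A reader might infer that the saliva comparison cannot assess any impact at all; the documents do not support that, because persistence at about 12 months is a legitimate question and the samples address it.

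It is also fair to say that the rebound statement comes from earlier work under other regimes. Here the antiseptic follows treatment of decay and is combined with sealants, so rebound could be slower. The document makes an unchanged count the expected result, not a certain one. But if rebound were slower because of the restorations and sealants, that would be an effect of the package and not of the antiseptic.

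Nothing in the protocol says that an unchanged count will be called a failure or that a fall will be credited to povidone-iodine alone. The hypotheses cover caries incidence and cost only, and no decision rule is attached to saliva. A reader might infer that a wrong conclusion is already planned; the text supports only the narrower point that the stated purpose invites one.

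Finally, the exponential model restates the return to baseline in numbers and is not independent evidence. That is correct, and the verdict does not depend on it.

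**Conclusion.** The point holds in a limited form. The year 2 and 3 samples, compared with baseline, can test whether salivary counts remain lower at the end of an annual interval after the whole programme. They cannot show whether, how much or for how long the antiseptic lowered counts, because no sample falls inside the period in which the document expects an effect. A fall cannot be attributed to the antiseptic, because the comparison is uncontrolled and other treatments come between samples.

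This rests on two things: the Background's own statement about return to baseline, and the inference that follow-up saliva is taken before re-application. If it were taken after re-application at the same visit, the comparison would be an immediate reading, and the text would have to say so.

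The consequence is confined to one secondary outcome. The primary caries comparison, the stated hypotheses and the economic model are not affected.

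**What to change.** 1. In Secondary outcome variables and in the Discussion, restate the purpose as: *persistence of any change in salivary counts at the annual visit (before re-application) after the whole programme*. This also settles the order of sampling and re-application, which is now only implied.
2. In interpreting the result, do not read no change as absence of an antiseptic effect between visits, and do not attribute a fall to the antiseptic alone.
3. Report counts by time since last application, so that children with only the second follow-up (about 24 months after their only application) are not pooled with those sampled at about 12 months.

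The cost is a few words and one variable derived from application and sampling dates. No extra visit is needed. The real downside is that the trial gives up a component-specific claim on a secondary outcome. To describe the short-term course of counts, the study would need a sample soon after application, which is hard to arrange with annual team visits to a remote area. Without a comparison group, even that sample would not separate the antiseptic from the other treatments.

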### Covariates

The relationship between the primary and secondary outcomes and the preventive intervention will be adjusted for known risk factors for dental caries - oral hygiene behaviours and diet (sugar consumption).

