### Analysis

All baseline socio-demographic characteristics will be described for the selected sample using counts and frequencies. Baseline and follow-up caries experience and questionnaire related information will be reported. Dental caries increment (incidence) will be the main outcome measure used to determine the effectiveness of the preventive intervention. The expected caries increment will be modelled from the three oral health surveys conducted in this community (2004; 2012 and 2015) and compared with the actual caries increment from 2015–2016; 2016–2017 and 2015–2017. The mean caries increment will be compared between the expected (modelled) and actual findings, and adjusted for known risk factors for dental caries. The hypothesis will be that caries increment observed in the period of 2015 to 2017 is smaller than the modelled caries increments. Two independent samples *t*-test will be used for the analysis with significance being determined if *p* < 0.05.

Children who receive only a part of the intervention will be separately assessed: for example we will have children who fully participate, those with baseline and only a year 1 follow-up, those with baseline and only a year 2 follow-up. This will ‘naturally’ further inform us on the most appropriate frequency of this preventive strategy. Both a group and matched analysis will be conducted to account for children who receive only part of the intervention.

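### Saliva change from baseline is read as the effect of the antibacterial component, while the secondary-outcome adjustment set omits age, so 1–2 years of growing up is mixed into the result

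*Protocol article*

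**What the plan says.** All statements are in the Protocol article.

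- **Study design:** no control group is formed. Non-consenting children may act as natural controls, but only through a dental examination at the end of the study. No saliva or quality-of-life data are mentioned for them. Age and residential history (fluoridated water) are collected by questionnaire.
- **Analysis:** a substitute comparator exists for caries: "The expected caries increment will be modelled from the three oral health surveys conducted in this community". None is described for saliva or for the quality-of-life scores.
- **Secondary outcome variables, saliva:** samples are repeated in years 2 and 3, and "Findings will be compared to baseline to assess the impact of the less frequently applied anti-bacterial component of the intervention".
- **Secondary outcome variables, quality of life:** "Oral Health-Related Quality of Life (OHRQoL) will be measured at baseline and at years 2 and 3". No comparator is named.
- **Covariates:** "The relationship between the primary and secondary outcomes and the preventive intervention will be adjusted for known risk factors for dental caries". The factors listed are oral hygiene behaviours and sugar consumption. Age is not among them.
- **Intervention:** on what drives salivary counts, "The number of teeth, fillings and other retentive sites in mouth influence the bacterial load".
- **Study participants and Aims:** children are 4–17 years old at entry, and the follow-up of interest is 1 and 2 years after the intervention.

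**The concern.** When every child is treated and no expected value is defined, the only relationship between an outcome and the intervention that can be estimated is change from the child's own baseline. That change includes whatever happens as the same children become 1 or 2 years older.

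For saliva the protocol supplies the mechanism itself: bacterial load depends on teeth and retentive sites, and these change as primary teeth are shed and permanent teeth erupt. The Markov model section places the start of mixed dentition at age 6, and the Background gives a mean decayed score of 3.43 at that age in 2012. Many of the teeth involved are therefore decayed.

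The Covariates section does not leave the choice open. It names one set for primary and secondary outcomes alike, chosen as caries risk factors. Ageing could be reported as an antibacterial effect, or could hide one. The Background says that mutans streptococci counts return to baseline within a few months, so a lasting effect at 1–2 years may be small and even modest drift could matter.

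**Working it through.** The plan states no figure to reproduce: no power calculation was done, and no SD, effect size or age trend is given for saliva or quality of life. The following is an illustration under stated assumptions.

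**Inputs.** From the protocol: gap of 1 or 2 years; ages 4–17; 339 children (the 2012 survey count, used as an illustrative n); 0.05 level (stated there for the caries test only). Assumed: two-sided test, unit SD, within-child correlation ρ = 0.5 (range 0.3–0.7), linear age trend g of 0.02, 0.05 or 0.10 SD per year, and zero intervention effect.

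**Before-after test.** The SD of change is √(2(1−ρ)) = 1.00 at ρ = 0.5, so SE = 1/√339 = 0.0543. Drift is d = g × gap. The rejection probability is Φ(d/SE − 1.96) + Φ(−d/SE − 1.96). For a 2-year gap:

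- g = 0.02: d = 0.04, d/SE = 0.74, rejection 11%
- g = 0.05: d = 0.10, d/SE = 1.84, rejection 45%
- g = 0.10: d = 0.20, d/SE = 3.68, rejection 96%

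For a 1-year gap the drift halves, and the rates are about 7%, 15% and 45%.

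**Range over ρ from 0.3 to 0.7, by total drift:**

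| n | d = 0.05 SD | d = 0.10 SD | d = 0.20 SD |
|---|---|---|---|
| 200 | 9–15% | 22–45% | 67–95% |
| 339 | 12–22% | 34–66% | 88–100% |
| 600 | 18–35% | 54–89% | 99–100% |

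**Does the stated adjustment help?** In 1,000 simulated trials (n = 339, ρ = 0.5, 2 years, hygiene and diet without an age trend), adjusting for hygiene and diet left a mean estimate equal to the drift: 0.05, 0.10 and 0.20 SD, with rejection of about 16%, 46% and 96%. These covariates can remove only the part of ageing that acts through them.

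**Does age help?** Adding age gave a mean estimate of 0.00 SD and rejection of 4–6%. Age can be separated from visit because ages are widely spread at baseline. With child fixed effects it could not be, since every child ages by the same amount between visits. A calendar-time term cannot help either, because it coincides with the intervention.

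**Price.** The unadjusted 95% half-width is 1.96 × 0.0543 = 0.106 SD. With age it was 0.109 SD at 1 year (0.109/0.106 = 1.03) and 0.116 SD at 2 years (0.116/0.106 = 1.09).

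**What breaks the age model.** Suppose there is no ageing effect, but outcomes differ by g per birth year. The baseline age slope is then −g, the model predicts a 2-year change of −2g, the true change is 0, and the visit coefficient is biased by +2g. With SE = 0.116/1.96 = 0.059, biases of 0.04, 0.10 and 0.20 SD give rejection of about 10%, 39% and 92%. Simulation gave 8–10%, 40–41% and 91–92%, while the simple paired test stayed near 5%.

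**The case against.** Five points have force.

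1. **No test is stated for these outcomes.** The t-test and 0.05 threshold are attached to the caries increment, and modelling of secondary outcomes is commonly left to an analysis plan. This stands against reading the rejection rates as properties of the protocol; they only show what drift does to a before-after comparison. It does not answer the covariate list or the saliva sentence, both of which are written down.

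2. **Quality of life.** A reader might infer that the protocol openly credits quality-of-life change to the intervention. It does not: those scores are only said to be measured, and the link comes from the general sentence under Covariates. Attribution is explicit for saliva alone. A reader might also infer that quality of life has no comparator anywhere. In the cost utility analysis, QALYs built from CHU-9D are compared with a modelled non-intervention scenario, and utilities are shown by age group. The gap concerns the scores as secondary outcomes.

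3. **The slopes are assumed.** A trend of 0.10 SD per year means 13 × 0.10 = 1.3 SD between ages 4 and 17, and 0.05 means 0.65 SD. Shedding and eruption may push bacterial load in opposite directions, so net drift could be near zero. This stands: the size is unknown.

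4. **Cohort effects.** The Background reports fluoridation soon after 2004, erratic operation and shutdown since April 2011, with dmft about 50% lower at ages 4–9 in 2012. Children of different ages in 2015 therefore had different exposure. As shown above, age adjustment can then introduce a bias as large as the one it removes. This stands and limits the remedy.

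5. **The adjusted coefficient is not the programme effect.** It is tempting to call it that, but it still holds calendar-time change and regression to the mean. For saliva it also holds treatment of existing decay, since the baseline sample precedes that treatment.

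**Conclusion.** The point holds in limited form. As written, the plan interprets saliva change from baseline as the effect of one component, and fixes an adjustment set that cannot separate that change from ageing. The same weakness reaches the quality-of-life scores by inference only.

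The mixing is structural; its size and direction cannot be stated from the document. The illustrative range of about 11% to 96% false rejection rests on assumed linear trends of 0.02–0.10 SD per year, 339 children, correlation 0.5, a 2-year gap and a significance test that the protocol does not specify. Age adjustment removes the drift only if age differences between children in 2015 represent ageing within a child. These are secondary outcomes, so the primary caries comparison is not affected by this point, but the wording should be changed before the results are interpreted.

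**What to change.** 1. **Covariates:** for secondary outcomes, add age in a flexible form and, for saliva, the number and type of teeth present. Fit one repeated-measures model to all visits with a visit term and a child random effect or child-clustered standard errors. Do not use child fixed effects.
2. **Reporting:** give the visit coefficient as age-adjusted change from baseline, beside the unadjusted change. Do not label either one the programme effect.
3. **Secondary outcome variables:** reword the saliva sentence so that it describes change from baseline without attributing it to the antibacterial component.
4. **Sensitivity analysis:** repeat the model with residential fluoride exposure added, because the 2015 age groups differ in fluoridation history.

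**Cost:** analysis wording only. Age and residential history are already collected, and teeth present should be available from the dental examination. The interval becomes about 3–10% wider in the illustration, and the adjusted result depends on the cross-sectional age assumption. Calendar time, regression to the mean and treatment of existing decay remain unresolved and should be named as limitations.
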